#### Assignment of the Intervention

The collection of adherence data patterns in both groups at baseline is crucial to check whether adherence patterns are homogeneous between the groups before the intervention starts. In both groups, patients will use an electronic monitor for at least 21 days before randomization. At the end of the baseline period, the patients will be randomized 1:1 to either attend the medication adherence program (intervention group) or be part of the standard of care (control group; Figure 1). The randomization lists will stratify participants according to their cancer type and the time elapsed between PKI initiation and the time of inclusion (less or more than 30 days). The randomization sheet lists 1 (intervention group) or 0 (control group) and will be provided by an independent researcher from the Unisanté Research Support Unit. The randomization list established by Excel (version 2016, Microsoft) will be based on variable size block randomization to prevent predictability and ensure a balanced allocation to each group. After randomization, the patient, research team, pharmacy, and clinical team will all be aware of the assigned group.

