### Outcomes

#### Primary Outcomes: Randomized Controlled Medication Adherence Study

The primary outcome was global adherence, defined as the percentage of days with correct medication use of each subject. The sample size was calculated to ensure sufficient power to test the difference in the mean logit global adherence between groups (see the *Sample Size* section). Medication adherence will also be compared between groups following the three operational definitions defined by the EMERGE (European Society for Patient Adherence, Compliance, and Persistence Medication Adherence Reporting Guideline) guidelines: implementation of treatment during the persistent period (daily management of oral targeted anticancer drugs), persistence with treatment (the distribution of times between enrollment and discontinuation), and longitudinal adherence (the product of persistence and implementation) [14,28,29].

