### Sample Size

#### Randomized Controlled Medication Adherence Study

We assumed that the mean longitudinal adherence will remain stable at 95% in the intervention group during the follow-up period, whereas it would decrease from 95% to 80% in the control group during the 340 days from randomization to the end of follow-up. We also assumed an SD for the logit of longitudinal adherence of 1.8, for both groups and at all timepoints. This corresponds to 95% individual adherence in the intervals 10%-99.3% and 35%-99.9% in the control and intervention groups, respectively, at the end of follow-up. A sample size calculation was performed to simulate individual series of daily medication (1=at least the correct number of daily openings of the electronic monitor; 0=fewer daily openings than prescribed) according to the above parameters to consider both the interindividual variability (SD 1.8) and the intraindividual variability (the measurement error). Considering that the number of measures of a subject will be 340 and assuming a 10% dropout in the middle of the year, 120 patients must be included in the study (60 in each group) to reach a power of 80% with a .05 significance level when comparing the mean of the logit of global adherence between groups using a two-tailed Student *t* test. Differences are considered statistically significant if *P*<.05.

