### Data Analyses

#### Medication Adherence Analysis

Adherence to PKI will be assessed using electronic monitor, calculated pill counts, and patient reports. Medication behavior will be described with a binary variable (1=at least the correct number of daily openings of the electronic monitor; 0=fewer daily openings than prescribed) in each group. This coding method is commonly used; however, this code cannot discriminate overadherence, which is considered in the same way as optimal adherence. The implementation will be described in each group using generalized estimating equation models; persistence with PKI (ie, adherence until PKI discontinuation) will be represented using a Kaplan-Meier survival curve [14]. Global adherence will be estimated in each group with the proportion of patients with correct medication taking, defined as ≥95% days with correct dosing during days 1 to 360, compared between groups using a chi-square test. As ≥95% days with the correct dosing threshold is an assumption, we will perform sensitivity analysis with other thresholds such as 90%, 85%, and 80%. Multivariate logistic regression models will be used to evaluate whether any detected effect of the intervention remained after adjusting for potential sociodemographic or clinical confounders. As a secondary analysis, the difference in medication taking will be explored across genders.

A systematic computerized term search in the adherence reports of the intervention group will be performed to identify the most frequent variables affecting PKI adherence, and a regression model will be used to discover their association with adherence [35].

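### The pre-randomization monitor data are given no role beyond a homogeneity check; prespecified adjustment of the adherence comparison for them would add precision at almost no cost

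*Protocol article*

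**What the plan says.** Under Assignment of the Intervention, the protocol article states: "In both groups, patients will use an electronic monitor for at least 21 days before randomization". The stated purpose is: "The collection of adherence data patterns in both groups at baseline is crucial to check whether adherence patterns are homogeneous between the groups". Allocation is then 1:1. The stratification factors are cancer type and time since the start of the protein kinase inhibitor (PKI); baseline adherence is not among them.

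Under Primary Outcomes the endpoint is fixed: "The primary outcome was global adherence, defined as the percentage of days with correct medication use of each subject". The Sample Size section obtains 120 patients for 80% power "when comparing the mean of the logit of global adherence between groups using a two-tailed Student" t test. The Medication Adherence Analysis section compares the proportion of patients at or above 95% correct days over days 1 to 360 with a chi-square test. It then adds multivariate logistic models to see "whether any detected effect of the intervention remained after adjusting for potential sociodemographic or clinical confounders". Neither section mentions adherence before randomization, as a covariate or in a change from baseline.

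**The concern.** The baseline value is measured before allocation in everyone who is randomized, on the same device as the outcome. That makes it a natural covariate. Checking the arms for homogeneity is a weak use of it: after proper randomization a difference between arms can only be chance, and a check detects such a difference without correcting it. If the check showed an imbalance, the article gives no prespecified response, and any adjustment made then would look post hoc.

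Two things are at stake. One is precision: the planning assumptions put a large SD (1.8 on the logit scale) between persons, and a baseline measure may explain part of it. The other is protection of the single estimate from this trial against a chance difference in starting adherence.

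**Working it through.** **Inputs from the Sample Size section.** Intervention stable at 95%; control falling from 95% to 80% over 340 days; logit SD 1.8 in both groups at all timepoints; 340 daily measures; 10% dropout at mid-year; 60 per group; two-sided 0.05. The 21-day baseline comes from Assignment of the Intervention.

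**Input not in the documents.** The correlation between a person's underlying level at baseline and during follow-up (ρ). It is varied as an assumption. The baseline mean is taken as 95% with the same SD of 1.8.

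**Step 1: reproduce the plan.** With the control decline linear on the probability scale, the difference in logits averaged over 340 days is 0.934.
- Sample size: n per group = 2(1.96 + 0.842)² × 1.8² / 0.934² ≈ 59.
- Power at 60: standard error = 1.8 × √(2/60) = 0.329; 0.934/0.329 − 1.96 = 0.88; power 81%.
- Simulation of daily 0/1 series with dropout and an empirical logit (0.5 correction): 80-82%.

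The stated 60 per group and 80% power therefore reproduce. A decline linear on the logit scale gives only 66-67%, so the probability-scale reading is used.

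**Step 2: add the baseline covariate.** The empirical logit of 21 baseline days enters a linear model with arm. Because 21 days measure a person's level with error, the observed correlation r is below ρ. Closed form: standard error = 0.329 × √(1 − r²), and the total N giving the precision of 120 unadjusted is 120 × (1 − r²).

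| Assumed ρ | Observed r (simulated) | Closed-form power | Simulated power | 120 × (1 − r²) |
|---|---|---|---|---|
| 0 | 0 | 81% | about 81% | 120 |
| 0.3 | 0.25 | 84% | 82-83% | 113 |
| 0.5 | 0.41 | 88% | 86-87% | 100 |
| 0.7 | 0.58 | 94% | 93-94% | 80 |

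For example, at r = 0.41 the standard error is 0.329 × 0.912 = 0.300, and 0.934/0.300 − 1.96 = 1.15, which gives about 88%. In simulation the residual SD falls from about 1.76 to about 1.6 at ρ = 0.5 and 1.43 at ρ = 0.7. Null rejection rates of the adjusted model in separate runs were 4.1%, 4.5% and 5.6%.

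**Step 3: a weaker baseline.** If monitoring lifts baseline adherence to 98% (assumption), simulated power at ρ = 0.5 is 84-85%. If days after discontinuation count as zero (assumption; the article is silent), r at ρ = 0.5 falls to 0.25-0.33 and the gain is 2-3 points.

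**Step 4: chance imbalance.** With an SD of 1.8 at baseline, one standard error of imbalance between groups in underlying level is 1.8 × √(2/60) = 0.33 logits. At ρ = 0.5 it shifts the unadjusted difference by 0.5 × 0.33 = 0.16 logits, against a target of 0.93, or about one sixth.

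**The case against.** The strongest reply is that nothing is wrong. The unadjusted t test is valid, the stated sample size meets its target, and a condensed article may leave the covariate list to a fuller document. The list of possible confounders is also open-ended. The first part stands in full: this is a matter of efficiency. The second stands only in part, because the article does state the tests, the purpose of the baseline and the type of adjustment, so the comment addresses a stated choice.

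The reply also limits how much can be promised:
- The SD of 1.8 belongs to longitudinal adherence, which includes persistence. The feasibility study in the Background had 97% implementation but 85% persistence at 12 months, and three weeks on treatment need not predict later discontinuation.
- A 21-day baseline falls within the six-week Hawthorne period named under Limitations of the Study.
- Some patients enter within 30 days of starting treatment and may not have settled.

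A reader might infer several stronger claims that the documents do not support:
- That power would rise above 99% under the plan's own model. This needs ρ = 1 (observed r about 0.84). The Sample Size section gives an SD at each timepoint but no correlation over time.
- That baseline adherence is the strongest available predictor. This is plausible but undocumented.
- That the homogeneity check is a decision step. The article attaches no test, threshold or action to it.
- That the baseline days certainly lie outside every outcome. Since 21 + 340 = 361, days 1 to 360 in the chi-square comparison might include them.

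**Conclusion.** The point holds as a recommended improvement. The article collects a pre-randomization measure of the outcome in every randomized patient and states no use for it beyond a check between groups. Adjusting for it takes power at 60 per group from about 80% to 86-87% at an assumed person-level correlation of 0.5 and to 93-94% at 0.7. The gain is small at 0.3 (82-83%), and at 0 power is essentially unchanged (about 81%), so there is little to lose. These figures rest on the plan's own effect and SD, a decline linear on the probability scale, and a correlation that the documents do not give. They do not make the t test invalid or the sample size of 120 wrong.

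**What to change.** Before the control-group monitor data are released for analysis:
1. Prespecify the primary analysis as a linear model of the logit of post-randomization global adherence on arm and the logit of pre-randomization adherence, with one stated correction for 0% and 100% applied to both.
2. State that the outcome window starts at randomization, so that baseline days cannot enter the outcome.
3. Report baseline adherence by arm descriptively.
4. Use the same covariate in the GEE and logistic comparisons.

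The covariate is already collected, so the cost is one degree of freedom and a sentence or two of text. The sample size need not change.

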Sociodemographic data and quality of life and beliefs about medication of patients who refused to participate and completed both questionnaires versus those who accepted to participate in the adherence study will be compared at baseline. For patients included in the adherence study, the results of the questionnaires will be compared at randomization, 6 months, and at the end of the study. Changes in *Belief about Medicines Questionnaire* and *European Organization for Research and Treatment of Cancer Quality of Life Questionnaire* or the *Treatment Satisfaction with Medicines Questionnaire* will be described longitudinally for the included patients and transversely per group at 6 and 12 months. Medians and IQRs or proportions will be used as appropriate. Nonparametric tests (eg, Mann-Whitney-Wilcoxon) or Fisher exact test of two proportions will be used to test the differences between groups.

Ultimately, the adherence patterns and their relationship with drug exposure and clinical response will be evaluated in an exploratory analysis.

To minimize interpretation bias, the statistician will not be aware of the group assignments during the analysis. The data will be analyzed in an intention-to-treat manner. All statistical analyses will be performed using the R statistical package (version 3.6, The R Foundation for Statistical Computing) [36].

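### Monitored adherence before randomization and the stratification factors are left out of the stated tests of global adherence; pre-specified adjustment would cost no new data and could add power

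*Protocol article*

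**What the plan says.** In the protocol article, *Assignment of the Intervention* has both groups use the monitor for at least 21 days before randomization and describes these data as "crucial to check whether adherence patterns are homogeneous between the groups before the intervention starts". No other use is stated there. The same section says "The randomization lists will stratify participants according to their cancer type" and adds a second factor, time from PKI initiation to inclusion (below or above 30 days).

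Two between-group tests are named for global adherence:

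- *Sample Size* powers the trial for "comparing the mean of the logit of global adherence between groups using a two-tailed Student" t test.
- *Medication Adherence Analysis* compares the proportion of patients with at least 95% correct days by chi-square test.

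Neither is described with covariates. The one adjusted comparison of the groups is a multivariable logistic regression to "evaluate whether any detected effect of the intervention remained after adjusting for potential sociodemographic or clinical confounders". Its covariates are not listed.

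**The concern.** The sample size assumes a between-patient SD of 1.8 on the logit scale. With 340 daily observations per patient, that spread makes up nearly all the variance of the outcome. A patient's own adherence before randomization is a natural candidate to explain part of it, and it is already collected.

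Looking at baseline homogeneity does not use this information. Under randomization any baseline difference is due to chance. Inspecting it neither corrects the estimate nor narrows its standard error, and no action is stated if an imbalance appears. Adjustment fixed in advance does both.

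The planned logistic model does not fill the gap. It works on a dichotomized outcome and is framed around an effect already detected, so it cannot recover precision in the main comparison. At stake is the chance of missing a real effect in a trial planned for 80% power.

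**Working it through.** **Inputs from *Sample Size*.** 60 per arm, two-sided alpha 0.05, 80% power; logit SD 1.8 in both groups at all times; 340 days; 10% dropout at mid-year. Intervention arm: "the mean longitudinal adherence will remain stable at 95% in the intervention group during the follow-up period". Control arm: "it would decrease from 95% to 80% in the control group during the 340 days from randomization to the end of follow-up". **From *Assignment of the Intervention*:** at least 21 baseline days. **Not in the documents:** the correlation ρ between baseline and follow-up logit adherence, which is therefore varied.

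**Step 1: reproduce the plan's figure.** If control adherence falls linearly from 95% to 80%, the logit difference averaged over 340 days is 0.931. Then

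n per arm = 2 × (1.960 + 0.842)² × 1.8² / 0.931² = 58.7, so 59, and power at 60 per arm is 80.9%.

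Simulating daily binary data with 10% of patients cut at day 170 gives 80.5%. The planned 120 is reproduced.

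**Step 2: closed form with adjustment.** Take the design as exactly 80% at 60 per arm. The detectable difference is 1.8 × 2.802 × √(2/60) = 0.921. ANCOVA replaces the SD by 1.8 × √(1 − ρ²), and the n per arm for 80% power becomes 60 × (1 − ρ²).

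| ρ | Residual SD | Power at 60 per arm | n per arm for 80% |
|---|---|---|---|
| 0 | 1.80 | 80% | 60 |
| 0.2 | 1.76 | 82% | 58 |
| 0.4 | 1.65 | 86% | 51 |
| 0.6 | 1.44 | 94% | 39 |

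**Step 3: simulation with the plan's inputs and 10% dropout.** Baseline and follow-up patient effects are normal with SD 1.8, and a chosen share of their variance is stable over time. Both outcome and covariate are empirical logits, log[(x + 0.5)/(n − x + 0.5)], the covariate from 21 days. The last column raises baseline adherence by 1 logit (an assumed size) to mimic the Hawthorne effect described in *Limitations of the Study*. Ranges are over repeat runs; Monte Carlo error is about 1 point near 80%.

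| Stable share | Baseline/follow-up correlation | t test | ANCOVA | ANCOVA, baseline raised |
|---|---|---|---|---|
| 100% | 0.84 | 79–81% | about 100% | 99–100% |
| 75% | 0.62 | 79–81% | 95–96% | 91–94% |
| 50% | 0.41 | 79–81% | 87–88% | 84–86% |
| 25% | 0.20–0.21 | 79–82% | 80–83% | 79–82% |

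With no correlation, ANCOVA loses nothing material (82.6% against 82.7% in one run). The simulation and the closed form agree.

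**Step 4: the shape of the decline.** If control adherence falls linearly on the logit scale instead, the difference is 0.779 and closed-form t-test power at 60 per arm is 66%. Adjustment still helps: in simulations where the correlation was 0.59 to 0.84, t-test power was 66–74% and ANCOVA power 91–99%.

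**Strata.** No prognostic strength is given for cancer type or time since initiation, so their contribution cannot be computed.

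**The case against.** *The unadjusted test is valid, so nothing is wrong.* This stands. After 1:1 randomization the t test is unbiased, and stratified allocation makes it at most conservative. The planned 120 reproduces, and 130 patients had entered the adherence part by June 2021. The point is about efficiency.

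*Covariates are usually left to the SAP, and the t test is named in the sample size section alone.* This stands in part. The article does not say that baseline data serve only as a balance check, and the logistic model's clinical confounders could include cancer type or baseline adherence. The text also sets no explicit significance gate for that model. Even so, the tests it does name are unadjusted, and the adjusted model it does name is on a dichotomized outcome.

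*The gain is assumed.* This stands as a limit on size. At a correlation of 0.2 it is almost nil. The minimum 21-day baseline lies wholly within the 6 weeks in which *Limitations of the Study* expects a Hawthorne effect. There is also a ceiling: under the plan's inputs about 39% of patients would show 21 correct days out of 21. If discontinuation also counted against global adherence (assumed at 15%, from the 85% persistence in the feasibility study, and unrelated to baseline), then at 50% stable variance power would be about 61% unadjusted and 66% adjusted.

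Three stronger readings are tempting but unsupported:

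- That power would approach 100%. This needs patient behaviour to stay fully stable for a year.
- That leaving out the strata makes the standard error too large. This holds only if they are prognostic.
- That the questionnaire analysis has the same fault. The article plans nonparametric or Fisher tests between groups, but it also compares results at randomization and describes change over time. These are supportive outcomes with no stated power.

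**Conclusion.** The point holds as an improvement to the primary analysis, not as an error. The stated tests of global adherence use neither the pre-randomization adherence nor the stratification factors, and the one adjusted model does not restore the lost precision. With the plan's inputs, 10% dropout and 60 per arm, power rises from about 80% to about 87% at a correlation of 0.4 and about 96% at 0.6, with almost no gain at 0.2 and no material loss at zero.

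These figures rest on an assumed correlation, a linear fall in control adherence, and an outcome that covers monitored days only. The Hawthorne effect may lower them. Any gain from the strata is additional and unknown.

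**What to change.** Before control-arm monitor data are released, pre-specify the primary analysis as an ANCOVA of empirical-logit global adherence over post-randomization days. The terms are arm, baseline empirical-logit adherence, time since PKI initiation (less or more than 30 days) and cancer type, with sparse types pooled by a stated rule. Run it whatever the unadjusted result, and keep the t test and chi-square test as sensitivity analyses.

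State the outcome window. The chi-square analysis covers days 1 to 360, while the sample size counts 340 days from randomization. If day 1 is enrollment, about 20 baseline days (360 − 340) would fall inside the outcome and overlap the covariate.

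Adjusting the questionnaire scores for the inclusion score is an optional secondary suggestion.

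The cost is a dated amendment or SAP entry. No new data or visits are needed. Because the trial is open-label and analysis was planned for 2022, the date matters; the concealment of control-arm monitor data until study end makes a credible pre-specification possible.

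### Allocation is stratified by cancer type and time since PKI start, but the powered t test and the chi-square test omit these factors, and the only adjusted model is a check on an effect already detected

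*Protocol article*

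**What the plan says.** Under Assignment of the Intervention, the protocol article describes 1:1 allocation in blocks of variable size: "The randomization lists will stratify participants according to their cancer type and the time elapsed between PKI initiation and the time of inclusion", the second factor being split at 30 days.

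The Sample Size section for the randomized part says that 120 patients are needed "to reach a power of 80% with a .05 significance level when comparing the mean of the logit of global adherence between groups", and names the test as "using a two-tailed Student" t test. No stratum or covariate enters that comparison.

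Under Medication Adherence Analysis:
- The proportion of patients with at least 95% correct days is compared by a chi-square test, with no strata.
- Implementation is described by GEE models, with no covariates named.
- Persistence is displayed as a Kaplan-Meier curve, with no test named.
- Multivariate logistic models are used to see "whether any detected effect of the intervention remained after adjusting for potential sociodemographic or clinical confounders". The stratification factors are not named there.

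**The concern.** Blocking within strata forces the arms to be nearly balanced on the stratification factors. Variation in adherence between strata then contributes almost nothing to chance differences between the arms. A plain t test does not know this: its standard error uses the whole between-patient variance, including the part that the design has removed. If the factors are prognostic, the standard error is too large, the P value is too large, and precision that the design has already paid for goes unused.

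The one adjusted analysis does not repair this. It works on the dichotomized outcome, so it never touches the logit-scale comparison on which the trial is powered. Its wording also makes it follow a positive finding. Read literally, it can cast doubt on an effect that was seen, but it is not called on when the unadjusted test has missed one.

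**Working it through.** **Inputs from the article (Sample Size).** Two-sided alpha 0.05 and power 80%. Intervention: "mean longitudinal adherence will remain stable at 95% in the intervention group". Control: "decrease from 95% to 80% in the control group during the 340 days from randomization to the end of follow-up". Spread: "SD for the logit of longitudinal adherence of 1.8, for both groups and at all timepoints". Dropout is 10% at mid-year, with 60 patients per group.

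**Assumed, because the article does not say.** R², the share of the variance of logit adherence explained by the two factors, is taken from 0 to 0.30. The simulation uses five cancer types, the largest about a third of patients (Results reports 43 breast cancer patients among 130, or 33%), crossed with two time strata.

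**Step 1: reproduce the 120.** Daily binary series over 340 days were simulated with person-level logit SD 1.8, a linear control decline on the probability scale, 10% dropout at day 170 and an unadjusted two-sided t test. With 60 per group, power is 0.804 (1,500 runs). A closed-form check takes the mid-course control value, 87.5%:
- difference = logit(0.95) − logit(0.875) = 2.944 − 1.946 = 0.999
- n = 2 × (1.8 × (1.960 + 0.842) / 0.999)², which rounds up to 52 per group
- 52 / 0.9 gives 58 per group, or 116 in total

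So 120 is the size for an unadjusted test with the full SD of 1.8. If the control decline is instead linear on the logit scale, simulated power at 60 per group is only 0.65. That is a separate sensitivity of the sample size and does not depend on the strata.

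**Step 2: what stratification does to the t test.** The difference that gives 80% power by the normal formula at 60 per group is 1.8 × 2 × (1.960 + 0.842) / √120 = 0.921.
- Standard error used by the t test: 1.8 × √(2/60) = 0.329, whatever R² is.
- Standard error under balanced strata: 0.329 × √(1 − R²), which is 0.312 at R² 0.10, 0.294 at 0.20 and 0.275 at 0.30. The simulation gives 0.292 at 0.20 and 0.279 at 0.30.
- Actual type I error: 2 × (1 − Φ(1.96 / √(1 − R²))), which is 0.039 at R² 0.10 and 0.028 at 0.20.

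**Step 3: simulation with stratified blocks.** N = 120, total SD 1.8, true difference 0.921, 5,000 runs per cell. The comparison is the t test against a linear model with main effects for both factors.

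| Assumed R² | Type I error, t test | Power, t test | Power, adjusted | Power forgone (points) | Closed-form adjusted power |
|---|---|---|---|---|---|
| 0 | 0.051 | 0.788 | 0.787 | about 0 | 0.80 |
| 0.05 | 0.047 | 0.799 | 0.806 | about 1 | 0.82 |
| 0.10 | 0.041 | 0.797 | 0.827 | 3 | 0.84 |
| 0.20 | 0.029 | 0.824 | 0.873 | 5 | 0.88 |
| 0.30 | 0.021 | 0.835 | 0.910 | 7 to 8 | 0.92 |

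Monte Carlo error is about 0.6 points for each power figure (√(0.8 × 0.2 / 5000)) and 0.3 points for each type I error. The adjusted model holds its type I error between 0.050 and 0.055 throughout.

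**Step 4: the wording of the adjusted analysis.** The powered comparison is linear, on the logit scale. The adjusted model is logistic, on a threshold of that outcome. Even if both stratification factors are among its covariates, the powered comparison stays unadjusted.

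**The case against.** The strongest reply is that this is a condensed article. Covariate lists are usually left to the full protocol or the analysis plan, and cancer type and time on PKI could well be among the clinical confounders mentioned. The t test appears only in the sample size section, and sizing on an unadjusted test does not forbid an adjusted primary model. This partly stands: the article does not exclude the strata from the logistic model, and their absence from an open list would not by itself be a finding. But the article does name its between-group tests, and both are unadjusted. It also ties its only adjustment to a detected effect and to the dichotomized outcome, and a longer covariate list changes neither of those.

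The second reply is that nothing planned is lost. This stands. The 120 were sized for the unadjusted test, and its simulated power stays at about 80% or above. What is forgone is a gain, and the error is in the safe direction. If the strata do not predict adherence, there is no gain.

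Three stronger readings are tempting, and the article does not support them:
- A reader might infer that a Kaplan-Meier comparison ignores the strata. Primary Outcomes says that persistence will be compared, but the only method given is a display, so there is no stated test to fault.
- A reader might infer that an effect will be claimed only if both the unadjusted and the adjusted tests are significant, and so compute a further loss of power. No such decision rule is stated. The logistic model can be read as a robustness check.
- A reader might infer that standard errors are certainly too wide. That depends on R², on which the article is silent.

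**Conclusion.** The point holds as a conditional inefficiency and a badly worded adjusted analysis, not as a threat to validity. The allocation uses two factors that the named tests ignore. With assumed R² of 0.10 to 0.20, the nominal 5% t test runs at about 4% to 3%, and 3 to 5 points of power are left unused. At R² 0.30 the figures are about 2% and 7 to 8 points; at R² 0 there is no loss. These sizes rest on the assumed R², on the assumed number and mix of cancer types, and on the article's SD of 1.8 with a difference that gives about 80% power. Choosing these factors for stratification suggests that some prognostic value was expected, but the article does not quantify it. The change is worth making because it costs almost nothing even when the factors turn out to be uninformative (power 0.787 against 0.788).

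**What to change.** Make the primary comparison a linear model for logit global adherence with treatment, cancer type and time since PKI start (less or more than 30 days) as fixed covariates. Pool rare cancer types by a rule set before the group assignments are linked to the adherence data: only 43 of 130 participants have breast cancer, so the rest may fall into small strata. Include the same two factors in the GEE model for implementation.

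State that the adjusted analysis is run and reported whatever the unadjusted result, and delete the wording "whether any detected effect of the intervention remained after adjusting for potential sociodemographic or clinical confounders". The unadjusted t test can stay as a supporting analysis.

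The cost is a change of wording and a few degrees of freedom: five in the simulated layout, out of 118 for the t test. No additional patients or data are needed, and the sample size of 120 need not be revised for this point.
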